## Abstract

**Background:**

*Trichuris suis* ova is a probiotic treatment based on the hygiene hypothesis. It has been demonstrated as safe and effective in autoimmune inflammatory bowel diseases and clinical trials indicate that helminth infections also have an immunomodulatory effect in multiple sclerosis.

We hypothesize that administering 2,500 *Trichuris suis* ova eggs orally every two weeks for 12 months is - due to its immunomodulatory and anti-inflammatory effect - significantly more effective than oral placebo in preventing new T2 and Gd+ lesions, as quantified by cerebral MRI and clinical examination, in relapsing-remitting multiple sclerosis and clinically isolated syndrome.

**Methods/Design:**

Fifty patients with relapsing-remitting multiple sclerosis or clinically isolated syndrome with clinical activity, not undergoing any standard therapies, will be randomized 1:1 to *Trichuris suis* ova 2,500 eggs every two weeks or matching placebo. The safety, tolerability and effect on disease activity and *in vivo* mechanisms of action of *Trichuris suis* ova in MS will be assessed by neurological, laboratory and immunological exams and magnetic resonance imaging throughout the 12-month treatment period and over a follow-up period of 6 months. Various immunological analyses will be used to assess the overall patient immune response prior to and at varying time points following treatment with *Trichuris suis* ova.

**Discussion:**

We anticipate that *Trichuris suis* ova will be well tolerated and more effective than the placebo in preventing new T2 and Gd+ lesions, as quantified by MRI. We also expect the Th1/Th17 proinflammatory response to shift towards the more anti-inflammatory Th2 response. This study has important clinical implications and will involve extensive research on the immunology of helminth therapy.

**Trial registration:**

ClinicalTrials.gov: NCT01413243

## Background

Multiple sclerosis (MS) is a chronic inflammatory disease of the central nervous system (CNS), whose incidence has increased over recent decades [1] and which features a specific geographical distribution with higher incidence rates in developed Western nations [2,3]. Although the etiology remains unclear, MS is widely assumed to be an autoimmune disease, in which both genetic susceptibility and environmental factors play a role [4]. In 1966, Leibowitz *et al.* first suggested that MS might be associated with high sanitation standards during childhood [5], and subsequent epidemiological surveys have confirmed high MS prevalence in regions where such standards are the norm [6]. Beneficial immunomodulation by helminths in humans has been demonstrated in an observational study of relapsing-remitting (RR) MS patients with asymptomatic, community-acquired gastrointestinal infections [7]. Compared with uninfected MS patients, parasite-infected patients showed a significantly lower number of exacerbations, stable disability scores, and fewer new T2 and gadolinium enhancing (Gd+) lesions in brain magnetic resonance imaging (MRI). Consequently, new treatment paradigms based on the hygiene hypothesis were developed for autoimmune diseases, including the administering of non-pathogenic live microorganisms. The first clinical trials using *Trichuris suis* ova (TSO), a pig whipworm that is non-pathogenic in humans, in autoimmune diseases, such as inflammatory bowel disease, showed good tolerability and a striking suppressive effect on the autoimmune response [8]. Recently, Fleming *et al.* completed a phase I controlled trial that showed significant reduction of disease activity in RRMS patients under treatment with TSO [9]. We have also analyzed the effects of TSO in four patients with secondary progressive MS and observed a slight down-regulation of the Th1-associated cytokine pattern, especially interleukin (IL)-2, with a temporary increase of Th2-associated cytokines, such as IL-4. Furthermore, mild eosinophilia and changes in CD4+ and CD8+ T cells and natural killer (NK) CD56 bright cell numbers were evident [10].

A number of different hypotheses currently seek to explain how helminths influence autoimmune disorders. An increase in IL-10 and transforming growth factor-β and a decrease in IL-12 and interferon-γ-secreting cells have been shown in fresh peripheral blood mononuclear cells (PBMCs) of MS patients with a helminth infection [7]. The patients also had a higher number of CD4+CD25+FoxP3+ regulatory T cells [7] and IL-10-producing CD19+ B cells [11]. The B cells also produced higher levels of brain-derived neurotrophic factor and nerve growth factor. In the MS animal model experimental autoimmune encephalomyelitis (EAE), a reduced incidence and delayed onset of disease after infection with *Schistosoma mansoni* was seen, probably as a result of down-regulation of proinflammatory cytokines [12].

Overall, this research suggests that TSO is a promising therapeutic option in RRMS. We plan to investigate this further in a monocentric, prospective, randomized, placebo-controlled, double-blind phase II pilot study in patients with RRMS or clinically isolated syndrome (CIS) [13] using MRI and clinical assessment, and hypothesize that oral administration of 2,500 embryonated TSO every two weeks is superior to placebo administration.

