### Blinding

Both the patients and all study personnel will remain blinded throughout the complete treatment period of 12 months. Treatment allocations will only be disclosed after the final database lock or in case of emergency. The active study therapy and placebo bottles will be supplied by OVAMED GmbH and labeling of bottles and randomization of patients will be performed in the central pharmacy of the Charité - Universitätsmedizin Berlin. The patients will mainly be attended to by a “treating physician”, responsible for evaluating the inclusion or exclusion criteria, adverse events, relapses, side effects and so on. All neurological examinations will be performed by an independent “evaluating physician”. To separate the physicians’ function in a threating and an evaluating position in order to prevent unblinding is necessary because patients under therapy with TSO commonly report gastrointestinal side effects that may point the physician to the verum therapy. Similarly, evaluation of all other paraclinical parameters, including MRI, will be conducted by independent examiners. Any patient-related crosstalk between treating and evaluating physicians or examiners will be prohibited unless required for safety reasons. A simple unblinding procedure has been designed, which allows for rapid unblinding of a patient in case of a medical necessity. If the patient is unblinded, he or she will be automatically excluded from the study.

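### Relapse evaluation sits with the treating physician in one section and with blinded evaluators in another, and nothing expressly keeps possibly revealing blood results from the treating physician

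*Protocol article*

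**What the plan says.** **Background.** The authors describe their own experience: "We have also analyzed the effects of TSO in four patients with secondary progressive MS". Among the findings were "mild eosinophilia and changes in CD4+ and CD8+ T cells". The article gives no count of affected patients and describes no comparison group.

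**Blinding.** The general statement is that "Both the patients and all study personnel will remain blinded throughout the complete treatment period of 12 months". The treating physician is "responsible for evaluating the inclusion or exclusion criteria, adverse events, relapses, side effects and so on". A separate evaluating physician performs the neurological examinations. The reason given for the split is that "patients under therapy with TSO commonly report gastrointestinal side effects that may point the physician to the verum therapy". Two broader safeguards follow: "evaluation of all other paraclinical parameters, including MRI, will be conducted by independent examiners", and "Any patient-related crosstalk between treating and evaluating physicians or examiners will be prohibited unless required for safety reasons".

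**Outcome parameters.** The primary endpoint is the cumulative number of new T2 lesions over 12 months. Annualized relapse rate and the proportion of relapse-free patients are secondary clinical endpoints. All clinical and MRI endpoints are to be assessed by evaluators who know neither the clinical data nor the allocation.

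**Table 2.** Safety laboratory tests and immunological sampling are both scheduled at months 3, 6, 9 and 12. The contents of the safety laboratory panel and the recipient of its results are not stated.

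**The concern.** Two things come together here. First, the article gives relapse evaluation to the one clinician whom it concedes may recognise active treatment from side effects. Elsewhere it says that every clinical endpoint is assessed by someone blinded to clinical data. Second, the article reports a laboratory change under TSO, repeats blood tests four times during treatment, and names only gastrointestinal effects as an unblinding clue.

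If the treating physician can infer the arm, the decision whether a reported worsening counts as a relapse, and whether an adverse event is attributed to treatment, may differ between arms. The annualized relapse rate, the relapse-free proportion and the tolerability comparison would then carry a bias that the analysis cannot remove.

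**Working it through.** The plan gives no figure on this point, so there is none to reproduce. The check is a comparison of sections, followed by an illustration under stated assumptions.

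**1. Who judges relapses?**

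- Blinding: the treating physician evaluates relapses, adverse events and side effects.
- Outcome parameters: evaluators of clinical endpoints, which include relapse rate and relapse-free proportion, are blinded to clinical data.

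A physician who handles side effects is not blinded to clinical data. Both statements cannot hold for the relapse endpoints. This step needs no assumption about blood results.

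**2. Is there a stated barrier between blood results and that physician?**

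- The independent-examiner sentence says who evaluates paraclinical parameters. It does not say that safety reports are withheld from the physician who must judge adverse events.
- The crosstalk rule says who may talk to whom, and it yields to safety, which is the purpose of a safety laboratory test.
- The treating physician evaluates eligibility, and Table 1 includes laboratory limits (white count, thrombocytes, liver and kidney values). That physician therefore probably sees laboratory reports at screening. That reports during treatment take the same route is an inference.
- Whether the safety panel includes a differential count is not stated. The haematology in Table 1 is haemoglobin, white count and thrombocytes only.

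**3. What can four patients show?** No number affected is reported. Exact (Clopper–Pearson) 95% limits for each possible number are:

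| Affected of 4 | 95% limits |
|---|---|
| 1 | 0.6% to 80.6% |
| 2 | 6.8% to 93.2% |
| 3 | 19.4% to 99.4% |
| 4 | 39.8% to 100% |

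For 4 of 4 the lower limit is 0.025^(1/4) = 0.398. The frequency under TSO is therefore almost unconstrained, and there is no placebo frequency at all.

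**4. Illustration.** Let pT and pC be the proportions with a raised count under TSO and placebo, with 1:1 allocation. A physician who sees the count guesses TSO when it is raised and placebo otherwise.

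- Chance that a raised count means TSO = pT / (pT + pC)
- Proportion of correct guesses = 0.5·pT + 0.5·(1 − pC) = 0.5 + (pT − pC)/2

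| pT (assumed) | pC (assumed) | Raised count means TSO | Correct guesses |
|---|---|---|---|
| 0.30 | 0.05 | 0.30/0.35 = 86% | 0.5 + 0.25/2 = 62.5% |
| 0.30 | 0.10 | 0.30/0.40 = 75% | 0.5 + 0.20/2 = 60% |
| 0.80 | 0.05 | 0.80/0.85 = 94% | 0.5 + 0.75/2 = 87.5% |
| 0.80 | 0.10 | 0.80/0.90 = 89% | 0.5 + 0.70/2 = 85% |

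If pT equals pC, the count carries no information and the result is 50%. These are rates of guessing the arm, not sizes of bias. The documents give nothing that would turn them into a bias in the relapse rate.

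**The case against.** The strongest case against is that the Blinding section already covers blood results in principle. They are naturally read as paraclinical parameters, which independent examiners evaluate, and crosstalk is banned. Routing of laboratory reports often sits in the full protocol or a laboratory manual, so silence in an article proves little. The outcomes concerned are secondary or safety outcomes in a pilot whose P-values are declared exploratory.

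Much of this stands, and it rules out three stronger readings that a reader might infer:

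- *The authors' data show that TSO causes eosinophilia.* A mild change in four patients with another disease course, with no comparator described, cannot show that.
- *The plan guards against gastrointestinal clues only.* These are the stated reason for the two-physician split. The two general safeguards reach further.
- *Routine blood results will unblind the study.* That needs a differential count on the panel and its delivery to the treating physician. Neither is stated. Nor do the documents support a claim about biased withdrawal decisions.

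What does not stand is the appeal to the article's brevity on roles. The article fixes the roles itself and fixes them inconsistently. One could reconcile the sections by supposing that the treating physician merely records suspected relapses and the evaluating physician decides. The text does not say so, and the treating physician would still influence which events are passed on.

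**Conclusion.** The point holds in a limited form. The conflict between the Blinding and Outcome parameters sections over who judges relapses follows directly from the text. The laboratory route is a possible additional source of unblinding that the stated safeguards do not expressly close. It rests on two assumptions: that a differential count or immunology result exists during treatment, and that the treating physician sees it.

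The exposure covers annualized relapse rate, relapse-free proportion and adverse-event attribution. It does not extend to the primary endpoint, because MRI is read by independent blinded examiners, nor to the neurological examinations, which the evaluating physician performs. Its size is unknown. The range of 60% to 88% correct guesses depends wholly on the assumed frequencies and on the physician seeing the counts. The change is worth making because it is cheap and protects the relapse comparison, not because harm has been demonstrated.

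**What to change.** 1. **Reconcile the two sections.** State in both Blinding and Outcome parameters that relapse endpoints are determined by the existing independent evaluating physician, who sees neither side effects nor blood results. The relapse definition requires duration, interval since the last event, and absence of fever or infection. The text should therefore allow these items alone to be passed on, for every suspected relapse, as a stated exception to the crosstalk ban.
2. **Cover laboratory results in the Blinding section.** State that any eosinophil or differential counts are masked on reports to treating and evaluating physicians, with an alert under a rule defined by the sponsor for safety. Other safety values are reported as now.
3. **Hold immunology results** in the laboratory until database lock. The abstract expects a shift towards a Th2 response under TSO, so these results are expected to differ by arm.

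Cost: a short revision of two sections, a laboratory report setting and someone to operate the alert. The evaluating physician is already in the design, and no samples are added. The downside is that the treating physician sees a mild eosinophil rise only through the alert. Whether that is acceptable, and where the alert is set, is for those responsible for safety to decide. If the full protocol already masks these counts, items 2 and 3 need only a sentence, and item 1 remains.

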## Methods/Design

### Trial design

TRIOMS is a monocentric, prospective, randomized, placebo-controlled, double-blind, phase II pilot study to be conducted at the Department of Neurology and the NeuroCure Clinical Research Center of the Charité - Universitätsmedizin Berlin. We plan to begin recruitment in Summer 2012. Fifty patients with RRMS or CIS, who have not undergone immunomodulatory treatment for at least 3 months, will be randomized to either TSO 2,500 ova or placebo to be taken every two weeks for 12 months as an immunomodulatory monotherapy. The detailed study design is based on the revised Consolidated Standards of Reporting Trials Statement [14,15].

The study is approved by the local ethics committee and the German competent authority (Federal Institute for Drugs and Medical Devices). The trial is registered at Clinicaltrials.gov (NCT01413243) and will be conducted in accordance with the Declaration of Helsinki in its currently applicable version, the guidelines of the International Conference on Harmonization of Good Clinical Practice (ICH-GCP), and the applicable German laws. All participants will be required to give written informed consent. The trial will be monitored according to ICH-GCP.

### Participants

The inclusion criteria for participation in the TRIOMS trial comprise the diagnosis of either definite RRMS according to the revised 2005 McDonald criteria [16] or CIS, an age of 18 to 65 years, a score of ≤4.0 on the Expanded Disability Status Scale (EDSS) [17], and disease activity on brain MRI (Table 1).

**Table 1 T1:** Eligibility criteria

**Key inclusion criteria**	Diagnosis of RRMS in accordance to the revised McDonald criteria (2005) or CIS
	Aged 18 to 65 years, inclusive
	Expanded Disability Status Scale (EDSS) at screening score ≤4.0
	Ability to provide written informed consent
	Disease activity on brain defined by:
	(A) ≥1 gadolinium enhancing lesion on screening MRI or another MRI performed in the 12 months prior to screening OR
	(B) ≥1 new T2 lesion on screening MRI or on another MRI performed in the 12 months prior to screening in comparison to an earlier MRI performed in the previous 36 months OR
	(C) ≥1 enlarging T2 lesion on screening MRI or on another MRI performed in the 12 months before screening in comparison to an earlier MRI performed in the previous 36 months
	Adequate birth control by a contraception method with a PEARL-index <1 in women of childbearing potential
	Contraindication or intolerance for established standard immunomodulatory treatments with interferon-β or glatiramer acetate
	Information about established standard immunomodulatory treatments for MS by an independent neurologist and explicit decision of the patient against these treatment
	Stable neurological state at study inclusion without any signs of a relapse and without steriod therapy in the last 30 days
**Key exclusion criteria**	Any disease other than MS that may better explain the symptoms and signs
	Any other immunomodulatory or immunosuppressive treatment, for example, interferon-β, mitoxantrone, glatiramer acetate, natalizumab within the preceding three months
	Any significant uncontrolled disease, such as neoplasia, relevant liver disorder, active hepatitis B or C, and reduced liver function
	Relevant laboratory findings:
	• aspartate aminotransferase/alanine aminotransferase (ASAT/ALAT) >3 times of reference value
	• bilirubine >1.5 mg/dl
	• hemoglobin <8.5 g/dl
	• white blood count <2.5/nl
	• thrombocytes <125/nl
	• creatinine-clearance according to Cockroft-Gault-formula <110 ml/min (male) and <95 ml/min (female)
	Any severe medical conditions or additional autoimmune disease which requires a immunosuppressive or immunomodulatory treatment
	Any psychiatric or other condition that impedes the ability to provide informed consent or patient’s compliance
	Refusal of transmission of personal data
	Inability to complete an MRI scan
	Relapse within 30 days of trial entry
	Known allergies against components of TSO or placebo
	Participation in any interventional clinical trial in the last three months or during the participant in TRIOMS
	Pregnancy or breast feeding
	Concomitant medication with antihelminthic therapy
	History of small intestinal resection

The main exclusion criteria include any disease course other than RRMS or CIS, any disease other than MS that may better explain the symptoms and signs, any immunomodulatory or immunosuppressive treatment, such as interferon-β, mitoxantrone, glatiramer acetate, natalizumab, within the preceding three months. Additionally, the participants must not have any significant uncontrolled disease, such as neoplasia or cardiovascular, renal, hepatic, endocrine or gastrointestinal disease or any other significant disease that may preclude the patient from participating in the study (Table 1).

### Randomization and interventions

The eligibility of patients will be determined at the screening visit. At the baseline visit, patients who qualified for participation in the study will be stratified according to gender and disease course (RRMS/CIS) and randomized 1:1 into the two intervention groups. One group will receive TSO 2,500 eggs orally every 14 days, the other a placebo suspension orally every 14 days. Visits will be carried out after 3, 6, 9 and 12 months (Table 2). To ensure reliable monitoring of tolerability, telephone check-ups are planned after every dispensation if a patient does not visit the study center, because prior studies have shown frequent gastrointestinal adverse events or symptoms after therapy with TSO [18]. Optional follow-up visits will be offered at 15 and 18 months after randomization. If necessary, additional unscheduled visits can be performed at any time.

**Table 2 T2:** Time schedule of regular study visits

	**Screening**	**Random (month 0)**	**Tel.V1 -6 (week 0, 2, 4, 6, 8, 10, 16, 20, 28, 32, 40, 44) ± 3 days**	**V1 (month 3) ± 10 days**	**V2 (month 6) ± 10 days**	**V3 (month 9) ± 10 days**	**V4 (month 12) ± 10 days**	**V5 (month 15) ± 10 days **** *(optional)* **	**V6 (month 18) ± 10 days **** *(optional)* **
Informed consent	x								
In/exclusion criteria	x	x							
Randomization		x							
Demographic data	x								
Pregnancy test	x								
Confirmation of MS diagnosis	x								
Relapse history	x	x		x	x	x	x	x	x
Medical history	x	x		x	x	x	x	x	x
Physical examination	x			x	x	x	x		x
Vital signs	x	x		x	x	x	x		x
Weight	x						x		x
MSFC	x						x		x
EDSS	x		x	x	x	x	x		x
Safety lab	x			x	x	x	x		x
Immunological sampling		x		x	x	x	x		x
MRI	x				x	x	x	optional	optional
AE/SAE				x	x	x	x	x	x
Questionnaires (fatigue, depression)	x	x			x	x	x	x	x
Drug supply		x	x	x	x	x			
Drug account					x		x		

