### Outcome parameters

The primary endpoint is the cumulative number of new hyperintense lesions identified on T2-weighted brain MRI during the treatment period of 12 months. Additional secondary MRI endpoints comprise the volume of T2 hyperintense lesions and number and volume of contrast-enhancing T1 hypointense lesions, the proportion of patients without any new T1 hypointense and T2 hyperintense lesions, brain atrophy as determined by brain parenchymal fraction and normalized brain volume 18 [19], and changes in brain metabolism (NAA/Cr-quotient) as determined by MR spectroscopy [20,21]. All MRI investigations will be performed using a 3 Tesla MRI scanner (Siemens Healthcare, Erlangen, Germany. Other secondary clinical endpoints include the annualized relapse rate and the proportion of relapse-free patients. A relapse is defined as *de novo* development, aggravation or re-occurrence of a pre-existing neurological abnormality compatible with MS, which lasts a minimum of 24 hours, is separated by at least 30 days from a preceding clinical event and does not occur in the context of fever or infection. Further secondary endpoints are the disease progression as determined by EDSS (evaluated by an independent neurologist) [17], Multiple Sclerosis Functional Composite (MSFC) [22], depression as determined by the Beck Depression Inventory (BDI) [23] and fatigue as determined by the Fatigue Severity Scale (FSS) [24]. Assessment of all clinical and MRI endpoints will be performed by experienced evaluators blinded to both the clinical data and treatment allocation. Peripheral venous blood (serum, heparinized blood for flow cytometry and PBMC isolation) will be sampled prior to and during the intervention to assess the effect on cellular and soluble components of the immune system. In detail, we plan to monitor the Th1/Th2/Th17 balance by concanavalin A stimulation of fresh heparinized blood and determination of cytokines using the cytokine bead array. In fresh heparinized blood, we will measure the frequency of B cells, CD4+ and CD8+ T cell subpopulations, innate immune cells and quantify the activation and homing markers on these cells by multicolor flow cytometry. We will also assess the number of IL-10-producing B cells by stimulation of fresh isolated PBMCs with 0.1 mg/ml CpG ODN2006 for 72 hr and will add phorbol myristate acetate and ionomycin (PMA+iono) for the last 6 hr and brefeldin A for the last 4 hr in order to block cytokine excretion. Detection of IL-10 producing cells is planned as intracellular staining of IL-10 on CD 19 expressing cells by multicolor flow cytometry. Alternatively, IL-10 we will be measured in the culture supernatants by ELISA with aliquots of supernatant taken from cell cultures before the addition of brefeldin A and PMA+iono to the cultures.

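### Table 2 schedules the pregnancy test at screening only and does not repeat it at month 0, where the criteria are re-checked and drug is first supplied

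*Protocol article*

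**What the plan says.** Table 1 (Participants) lists "Pregnancy or breast feeding" among the key exclusions. Its inclusion criteria set the age range, "Aged 18 to 65 years, inclusive", and require "Adequate birth control by a contraception method with a PEARL-index <1 in women of childbearing potential".

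The text under Randomization and interventions states: "The eligibility of patients will be determined at the screening visit". It goes on: "At the baseline visit, patients who qualified for participation in the study will be stratified". Screening and baseline are therefore separate visits, and Table 2 gives each its own column.

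The Table 2 rows that matter here:

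- "Pregnancy test": one mark, at screening, and none in any later column.
- "In/exclusion criteria": two marks, at screening and at month 0.
- Randomisation: one mark, at month 0.
- Drug supply: first marked at month 0.
- Medical history: marked at screening, at month 0 and at every later in-person visit.
- Vital signs and immunological sampling: both marked at month 0.

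**The concern.** The schedule repeats the eligibility check just before treatment starts, but it does not repeat the pregnancy test. Pregnancy is an exclusion that can arise between two visits. It can also be present at the first visit but too early to detect, and the woman may not know of it at the second. In those cases the last scheduled test before the first dose cannot find it.

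At stake is the exposure of a pregnant participant whom the plan means to exclude. Nothing statistical depends on this: the primary endpoint, the analysis methods, the fixed sample of 50 and the interpretation of the results stay as they are.

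**Working it through.** **Reading the schedule.** At month 0 Table 2 has a criteria check, randomisation, a first drug supply and a medical history. It has no pregnancy test there and none later. The article fixes this row by row, so the timing of the test is stated and not left open. The plan gives no figure on this point that could be reproduced.

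**Inputs for the size**

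- Women of childbearing potential: not given. Assumed 10 to 35 of the 50 patients. The low end allows for the upper age limit of 65, since some women will be past childbearing age.
- Pregnancy rate: Table 1 requires a Pearl index below 1. The ceiling of 1 is used, that is 0.01 pregnancies per woman-year.
- W, weeks from screening to month 0: not given. Assumed 2 to 12, with 4 as the working value.
- L, the lag in weeks from conception to a detectable result: not given. Assumed 1 to 3.

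**Formula.** If both tests share the same lag and the rate is constant, the screening test finds conceptions up to L weeks before screening, and a month-0 test finds those up to L weeks before month 0. The gap between the two limits is W weeks whatever L is, so L cancels:

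extra pregnancies found = women × 0.01 × W/52

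For example, 10 × 0.01 × 4/52 = 0.0077 and 35 × 0.01 × 4/52 = 0.0269.

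| Women | W = 2 | W = 4 | W = 8 | W = 12 |
|---|---|---|---|---|
| 10 | 0.0038 | 0.0077 | 0.0154 | 0.0231 |
| 25 | 0.0096 | 0.0192 | 0.0385 | 0.0577 |
| 35 | 0.0135 | 0.0269 | 0.0538 | 0.0808 |

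**What a month-0 test would still miss.** Conceptions in the last L weeks before month 0 number women × 0.01 × L/52. That is 10 × 0.01 × 1/52 = 0.0019 at the low end and 35 × 0.01 × 3/52 = 0.0202 at the high end.

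**Limits of the figures.** They are illustrative. Using the ceiling of 1 makes them high for women who adhere to the required contraception. They are not strict upper bounds, because a conception too early to show at screening may precede the use of that contraception.

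**The case against.** The strongest case against is that the plan is workable as it stands. The text places eligibility at the screening visit, and the pregnancy test is at that visit. Month 0 can be read as a confirmation step that need not repeat every test: the safety laboratory, which supports several laboratory exclusions, is also marked at screening and not at month 0. Contraception is required, and the history taken again at month 0 can bring out a known or suspected pregnancy. If baseline follows screening within days, a second test adds almost nothing, and a short maximum interval would be an alternative remedy. Finally, most exposure would occur later: at the same assumed rate, 12 months of dosing gives 10 × 0.01 = 0.10 to 35 × 0.01 = 0.35 pregnancies, against 0.008 to 0.027 for a 4-week window before the first dose.

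Most of this stands, and it is why the point is minor. It does not remove the point. Table 2 itself repeats the criteria check at month 0, a history cannot reveal a pregnancy the woman is unaware of, and the plan already tests at screening despite the contraception rule.

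A reader might infer more than the article supports:

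- *That the month-0 check has nothing behind it.* The screening result, the repeated history and the contraception criterion all stand behind it. What is missing is a repeat test.
- *That Table 2 contradicts the text or Table 1.* It does not. A test at screening is consistent with determining eligibility at screening.
- *That the interval between screening and baseline is uncontrolled.* The article gives no maximum, but the full protocol commonly holds it, so this cannot be concluded.
- *That pregnancy surveillance during treatment is deficient.* Table 2 marks no later test, but the exclusion is applied at entry and the article is condensed. The point is confined to the first dose.

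**Conclusion.** The point holds as a low-cost improvement to the stated schedule, for patient safety only. The pregnancy test is not repeated at the visit where patients are randomised and first supplied with drug, so a pregnancy that began after screening, or was undetectable then, could go unnoticed at the first dose. The expected gain is very small: about 0.01 to 0.03 pregnancies at 4 weeks, and 0.004 to 0.081 over intervals of 2 to 12 weeks. These results rest on assumed numbers of women, an assumed interval, a constant rate at a Pearl index of 1 and the same detection lag at both tests. The gain is proportional to the interval, which the article does not state. The case for the change rests on its low cost, not on the expected number of cases.

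**What to change.** In Table 2, mark a urine pregnancy test in the month-0 column for women of childbearing potential, and require a negative result before the first dose. The cost is one inexpensive strip per such woman, 10 to 35 strips under the assumption above, and one added mark in the table. Month 0 is already an attended visit, and blood "will be sampled prior to and during the intervention", so no extra visit, staff or invasive procedure is needed. Very recent conceptions would still be missed, as shown above.
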